### Inclusion and exclusion criteria

To clarify the inclusion and exclusion criteria, interviews will be conducted with all subjects via telephone (MINI, HRSD-24).

All MINI and HRSD-24 interviews will be conducted by the same two trained interviewers, who are a psychologist and a medical student. The training of the interviewers was delivered at the Charité Department of Psychiatry and Psychotherapy. Within this training, an opportunity to practise with depressive patients was provided, followed by a discussion regarding the ratings guided by a psychiatric consultant.

To be eligible, participants must (1) be between 18 and 65 years old, (2) have sufficient German language skills, (3) have uninterrupted access to the Internet, (4) score 12 or higher on the BDI-II, (5) provide their electronic data with the “declaration of consent” and (6) have a major diagnosis of a depressive episode or dysthymia (ICD-10: F32; F33; F34) (according to the MINI).

Subjects were excluded if they met one of the following criteria: (1) diagnosis of a bipolar disorder; (2) currently present psychotic symptoms or a diagnosis of an acute schizophrenic disorder (ICD-10: F2x; F31; F32.3; F33.3), acute substance dependence or withdrawal syndrome (ICD-10:F1x.2; F1x.3); or (3) they are currently experiencing or have experienced suicide ideations (operationalized via HRSD-24—subjects are excluded if they have a score of 3 or above on suicidality items) in the past.

A comorbid diagnosis other than depression is not an exclusion criterion, as the aim was to reflect routine care as realistically as possible. However, an active substance dependency is an exclusion criterion, as psychotherapy is not indicated during an active substance dependency as this limits any intervention (e.g. intoxication, concentration deficit, withdrawal symptoms). In addition, acute addiction could distort the effectiveness of the programme in patients with depression. Other primary psychiatric disorders are excluded as including these patients will reduce the internal and external validity of our trial, which targets the effects of the programme for patients with depressive disorder.

Subjects who do not meet our inclusion criteria due to the severity of illness are encouraged to seek professional help.

Adequate language skills are determined during the initial diagnosis by the MINI and HRSD-24. Our inclusion criteria were critically discussed in the study board.

### Randomization and blinding

Subjects who meet the inclusion criteria will be randomly allocated to one of the three groups: (a) immediate access to the unaccompanied depression course of “Selfapy”, (b) immediate access to the accompanied depression course of “Selfapy” or (c) access to “Selfapy” after a delay of 24 weeks (control group).

Block randomization is performed by an independent researcher using a random number assignment plan for this list, which was created by a computer-controlled random number generator. These numbers are assigned blindly, i.e. subjects and researchers have no knowledge of which group a patient was allocated to. The subjects are randomly assigned to one of the three groups in a ratio of 2:2:1. The subjects will be informed by email about the result of the allocation process. Subjects in one of the intervention groups received an email with a link and their respective access code to register and be able to start the intervention immediately. Subjects in the control group who also received an email with a link that leads the subject to the assessment material will be informed by email about the result of the random assignment. Therefore, participants enrolled themselves in the study programme. Diagnostic interviewers are blind to the assigned group of subjects. An illustration of the patient flow can be found in Fig. 1.

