### Accompanied group

In the accompanied version of the programme, the subjects are supervised by experienced psychotherapists in training throughout the duration of the programme. In the beginning, the expert and the subject get to know each other and consequently hold 20- to 25-min conversations by phone on a weekly basis. In the course of this conversation, the psychotherapists address the content from Table 1 in a structured manner. A special focus lies on discussing and reviewing the accomplishment of the exercises incorporated in each module*.* In a 1-h training session, all clinical psychologists who were interested in accompanying subjects were informed. The training included general information on the study, risks and handling of these risks, a discussion of the non-accident concept, instructions on the handling and documentation of drop-outs and information on the standardization of the discussion content.

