#### Secondary outcome measures

Changes in depressive symptoms will be additionally assessed at baseline (T1) and post (T3) after 12 weeks as well as at follow-up (T4) using observer-rated inventories HRSD-24 and the QIDS [25].

Furthermore, changes in the self-assessment of anxiety-related symptoms will be analysed using the BAI [26]. Changes in self-esteem will be evaluated using the SWOP-K9 [27]. Similarly, the SASS [28] questionnaire will be utilized to record the levels of social activation. The WHOQOL-BREF [29] will be used to assess the impact of the programme on physical changes and life satisfaction. The APOI captures attitudes towards online interventions [30].

The WAI [31] is an employment inventory for the collection of therapeutic alliances and is used to evaluate work alliances. The ACSA is a self-anchoring rating scale for subjective well-being that was originally developed as a simple method to measure the quality of life consecutively in the patient-physician relationship [32]. The Bado sheet is used to assess the impact of the programme on subjects’ use of the healthcare system, including contact with healthcare providers, the number of therapy sessions and the amount of contact with psychotherapists and psychiatrists.

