### Planned statistical analysis

The recorded data of the different measurement times (T1, T2, T3 and T4) for both intervention groups and the control group are analysed. The treatment results of all subjects (pre-post difference) are analysed using intention-to-treat (ITT) analyses.

The primary endpoint is the decrease in depressive symptoms in the BDI-II (Delta BDI-II) between study entrance (T1) and the end of the intervention (T3). A one-way ANOVA (within factor “group”) is performed to analyse the differences in the decrease of depressive symptoms between the intervention groups. A Bonferroni correction for multiple testing is applied to examine the expected group differences. This correction is carried out using the formula *α*/*n* (with alpha level *α* = 0.05 and *n* = number of tests) in order to lower the level of significance, make fewer results significant and thus the number of false-positive results reduce.

In an exploratory analysis, the basic effectiveness of the intervention compared to the control condition is examined (accompanied and unaccompanied group vs. control group) in order to counter the high drop-out rate.

In addition, the mean values including confidence intervals (95%) are recorded. The data are aggregated in the form of mean values and standard deviations. No interim analyses are planned.

To check the data obtained from the measuring instruments for normal distribution, the Kolmogorov-Smirnov test is calculated at the beginning. For this purpose, the mean values and standard deviations of each variable, as well as the Kolmogorov-Smirnov *Z*-value, are calculated, and the asymptotic significance (two-sided) is determined. Values below 0.05 indicate a violation of the normal distribution.

The intermediate measurements are analysed with regard to continuous outcome measures using repeated-measure ANOVAs. Independent *t* tests and *χ*^2^ tests are used to estimate the intergroup differences in sample characteristics prior to treatment.

Missing values in the data are replaced by multiple imputations, as well as “last-observation-carried-forward” (LOCF), “baseline-observation-carried-forward” (BOCF) and a “reference-based multiple imputation” method (“jump-to-reference” approach) to replace the missing values.

Effect size calculations to measure the therapeutic success (before and after the intervention) are carried out by dividing the difference between the respective group mean values by their pooled standard deviation.

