Effect sizes under 0.2 are deemed small, and 0.5 moderate and 0.8 are deemed large [36].

All data evaluations are carried out without knowledge of the political group affiliation (blinded data evaluation). That means the evaluating person does not know which expression of the group variable indicates the representation to the IG and which the rights to the KG.

An external team was built, in order to monitor and recheck the execution of the planned statistical analysis.

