## Abbreviations

ACSA: Anamnestic Comparative Self-Assessment
APOI: Attitudes towards Psychological Online Interventions Questionnaire
Bado: Basic documentation
BAI: Beck Anxiety Inventory
BDI-II: Beck Depression Inventory-II
CBT: Cognitive behaviour therapy
HRSD-24: Hamilton Depression Scale
CI: Confidence interval
iCBT: Internet-delivered cognitive behaviour therapy
MINI: Mini International Neuropsychiatric Interview
RCT: Randomized controlled trial
SASS: Social Activity Self-Assessment Scale
SMD: Standardized mean difference
SWOP-K9: Self-Efficacy, Optimism and Pessimism Scale
QIDS-SR: Quick Inventory of Depressive Symptomatology Self-Report
WAI: Working Alliance Inventory
WHOQOL-BREF: WHO Quality of Life-BREF

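### The trial is called blinded, but subjects and therapists know the arm, the primary outcome is self-rated, QIDS is misclassified as observer-rated, and coded labels cannot mask control

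*Protocol article*

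**What the plan says.** All places are in the protocol article.

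- **Label.** The title, the abstract's conclusion and the opening of the Discussion call the study blinded, without saying who is blinded.
- **Allocation.** Randomization and blinding says that the random numbers are assigned blindly, and explains this as: "subjects and researchers have no knowledge of which group a patient was allocated to". A little later in the same paragraph: "The subjects will be informed by email about the result of the allocation process". It also says that the diagnostic interviewers do not know the group.
- **Arms.** Under Accompanied group, therapist and subject "hold 20- to 25-min conversations by phone on a weekly basis". Under Unaccompanied group, subjects work alone with a chat for questions. Randomization and blinding gives control subjects access only after 24 weeks.
- **Outcomes.** Primary outcome measure names the self-assessed BDI-II. Secondary outcome measures says that depressive symptoms are additionally assessed "using observer-rated inventories HRSD-24 and the QIDS". The list of abbreviations has "QIDS-SR: Quick Inventory of Depressive Symptomatology Self-Report".
- **Analysis.** Planned statistical analysis states "All data evaluations are carried out without knowledge of the political group affiliation (blinded data evaluation"), explained as the evaluator not knowing which code stands for intervention and which for control. The same section plans intention-to-treat analysis, a pooled comparison of both active arms with control, and, among other imputation methods, "a “reference-based multiple imputation” method (“jump-to-reference” approach").

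**The concern.** An unqualified blinded label tells a reader that knowledge of the arm could not have shaped the outcome data. Here the primary outcome is a questionnaire filled in by people who have been told their arm. Subjects who know that they are waiting may report less improvement than they otherwise would, and subjects with a weekly therapist may report more. Both tendencies run in the direction of the main hypotheses.

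Calling QIDS observer-rated adds to this. Agreement between BDI-II and QIDS could be taken as confirmation by an independent rater, when both come from the same unblinded subject. The limitations in the Discussion cover heterogeneity, parallel use of healthcare and other primary diagnoses, but not unblinded self-report.

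The analyst blinding is the remaining safeguard that the article offers, so it matters how far it reaches.

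**Working it through.** Most of this is a comparison of statements. Arithmetic enters only for the coded labels.

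**1. Who knows the arm?**
- Subjects: informed by e-mail, and able to see which arm they are in from what they receive. Not blind after allocation.
- Therapists: those making the weekly calls know that they serve the accompanied arm. Not blind.
- HRSD-24 interviewers: stated to be blind. Inclusion and exclusion criteria says that the same two trained interviewers conduct all MINI and HRSD-24 interviews; I take the therapist-assessment label in Table 2 to mean them.
- Analysts: coded group variable (step 3).

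**2. Which depression outcomes are rated by someone blinded?**

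| Scale | Secondary/primary outcome text | Table 2 | Rater blinded? |
|---|---|---|---|
| BDI-II | self-assessed | self, T1–T4 | no |
| QIDS | observer-rated | QIDS-SR16, self, T1–T4 | no |
| HRSD-24 | observer-rated | interviewer, T1, T3, T4 | yes, as stated |

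The text implies two observer-rated depression scales; there is one. Its protection is limited. Interviews at entry are by telephone, and if those at T3 and T4 are too (not stated), a subject can still reveal the arm in conversation.

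**3. What can the coded labels hide?**

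Inputs from Sample size: N = 400, ratio 2:2:1, expected drop-out 50%.
- Randomised, each active arm: 400 × 2/5 = 160. Control: 400 × 1/5 = 80. These match the stated arm sizes.
- In the intention-to-treat set, control is the arm of half size, so its code is visible from a frequency count. The two arms of 160 cannot be told apart by size.
- Among completers, expected numbers are arm size × retention. The article gives no retention by arm, so the rows below are assumptions. The last column is the share of 200,000 binomial draws in which control was the smallest arm.

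| Retention control / accompanied / unaccompanied | Expected completers | Control smallest |
|---|---|---|
| 50 / 50 / 50% | 40 / 80 / 80 | effectively 100% |
| 70 / 60 / 50% | 56 / 96 / 80 | 99.9% |
| 91 / 91 / 50% | 72.8 / 145.6 / 80 | 84% |
| 91 / 50 / 50% | 72.8 / 80 / 80 | 71% |

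Size alone is thus less conclusive in completers if drop-out is very unequal. The planned analysis is intention-to-treat, however, where the half-size arm is plain.

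Two planned analyses also need the control arm designated whatever its size: jump-to-reference imputation, which must be told which arm is the reference, and the pooled active-versus-control comparison.

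**The case against.** **The sentence may describe allocation concealment.** It opens with the blind assignment of random numbers and follows directly on the random number list, and the e-mail to subjects is disclosed soon after. That reading is fair, and an attentive reader would see that subjects learn their arm. It does not rescue the unqualified label in the title, abstract and Discussion, and the wording still says that subjects do not know the group.

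**Analyst blinding is planned.** A reader might infer that it does not exist, or that the whole arm code can be recovered with certainty. The article supports neither. It describes a coded variable, nothing says that analysts receive decoded labels, and size cannot separate the two active arms, whose contrast is the second main hypothesis and the dismantling purpose. Jump-to-reference can be run by a second person, and who does so is detail that a full protocol or analysis plan may hold. What stands is narrower: the article defines its blinding as not knowing intervention from control, and that is the distinction that arm size gives away.

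**QIDS is an editorial slip.** Probably so, since Table 2 and the abbreviation list are right. It still changes how many observer-rated depression measures the article appears to have.

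**The bias has no stated size.** Correct. A reader might be tempted to assume a reporting bias and express it as a share of the planned d = 0.23. No bias figure is given, so such a share would only restate the assumption. Moreover, 0.23 was derived from unaccompanied programmes, whereas the Background expects larger effects with accompaniment.

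**The choice among imputation methods** is a separate matter and carries no weight here.

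**Conclusion.** The article claims more blinding than the design can deliver. Subjects and accompanying therapists are unblinded, and the primary outcome is self-reported by subjects who know their arm. HRSD-24 is the only depression outcome with a blinded rater, not one of two. Coded analysis can mask accompanied from unaccompanied, but not control at 80 against 160 and 160 in the intention-to-treat set.

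The size of any resulting bias cannot be derived from the documents. Its probable direction, towards the programme when compared with control, is a judgement about how subjects report and not a result shown here. The conclusion assumes that the e-mail goes out as described, that the interviewers remain blind as stated, and that the 2:2:1 ratio is kept.

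The design itself survives: an open, self-rated comparison with a waiting list is interpretable if it is described as such. The description should be corrected before results are reported.

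**What to change.** 1. Replace the blinded label in the title, abstract and Discussion by a description of who is blinded: open to subjects and therapists, blinded HRSD-24 interviewers, and group-coded analysis in which control is identifiable. As the article is published, this can go into the next protocol version and the main report; the Discussion already undertakes to disclose changes.
2. Reword the sentence on number assignment as allocation concealment, and say separately who stays blinded afterwards.
3. List QIDS-SR16 with the self-rated measures in Secondary outcome measures.
4. Add unblinded self-report of the primary outcome to the limitations, and report the HRSD-24 change from T1 to T3 beside BDI-II when drawing the conclusion. Note that subjects may disclose their arm to the interviewer.
5. Write and lock the analysis scripts on dummy labels before data release. Have the jump-to-reference step run by someone other than the blinded evaluator. If the external team is considered for this, note that its stated role is to monitor and recheck, and that executing a step would weaken that independence.

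Cost: the stated design quality becomes less favourable, and there is a little script work. No new assessment is needed, because HRSD-24 is already collected at T1, T3 and T4.

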**Fig. 1 Fig1:**
[figure not shown]
“Selfapy” programme flowchart

After successfully completing the MINI and HSDR-24, the unblinding of the researchers will be possible in the case of acute suicidality and before the study programme will be terminated for the respective participant.

### Intervention

“Selfapy” is a browser-based commercial programme for reducing depression symptoms (https://www.selfapy.de). To achieve this goal, the user receives instructions on evidence-based methods and exercises in the areas of CBT, system therapy, behaviour therapy and mindfulness training. The “Selfapy” programme is available in an accompanied and unaccompanied version.

Subjects in the intervention groups (accompanied and unaccompanied) have free access to the 12-week Internet-based self-help treatment. The online course is divided into 12 different modules. Every week, a new topic is discussed, such as “self-awareness”, “challenging negative thoughts” or “sociability”. The weekly modules consist of informative texts, videos, interactive exercises and worksheets. Table 1 contains the 12 module topics and a brief description of these and the exercises they contain. The programme also includes a so-called classroom by allowing the psychologist to follow the programme of the subjects. The “classroom” includes an integrated chat system through which psychologists and subjects can communicate.

**Table 1 Tab1:** Overview of course content

Module	Content	Exercises
Your beginning	A questionnaire is used to collect general data about this person and his/her problems.	Lifeline; problem cakes; miracle question
**Target selection**		
First insights	In this module, the user is brought closer to the connection between thinking, feeling and acting. Based on this triangular connection, our course concept is explained to him/her.	Your personal triangles
Resources	Power sources are explained and gathered. Different methods are introduced to assist users in collecting power sources. Behavioural activation is prepared.	Evaluation daily protocol; power source images; treasure chest; resource walk
Behavioural activation	How to actively plan power sources during the day is explained.	Activity plan
Automatic thoughts	Automatic thoughts and thinking patterns are addressed.	Automatic thoughts; core beliefs
Realistic thoughts	The content of this module focuses on thinking about reality and thinking realistically.	Think realistically
Self-esteem	A positive self-concept is important for overcoming problems. The user learns how the concepts of self-confidence and self-acceptance can help to develop a positive self-image.	Positive self-image
Self-efficacy	The user is made aware of recent successes. This will enable him or her to better allocate his or her power reserves and increase confidence in his or her abilities.	“Your personal achievements—be proud of yourself”
Solve problem	Training to perceive a specific problem, gather potential responses in a problematic situation and develop the competence to implement a particular course of action to solve this problem optimally is introduced.	Problem-solving training
Mindfulness + excursus: pleasure training	In this module, mindfulness is the focus. A mindful approach is cultivated to improve stress management.	Mental note; mindfulness in everyday life; sitting meditation; body scan; your enjoyment moments
Social environment + stigma + social support	The focus of this module is on the environment and the social environment of the user. How social support can help to deal appropriately and successfully with stress is clarified.	“Difficult communication—your backing”
Relapse cases	Finally, a tool is introduced to help the user recognize when stress increases and becomes too much and how to handle it when the stress cannot be avoided.	Risk situations; early warning symptoms; first aid plan; relapse protocol

Subjects are advised to spend at least 15 to 20 min a day on the programme. If the modules are not processed for 3 weeks (recorded via login), this will be counted as the subjects drop out.

### Accompanied group

In the accompanied version of the programme, the subjects are supervised by experienced psychotherapists in training throughout the duration of the programme. In the beginning, the expert and the subject get to know each other and consequently hold 20- to 25-min conversations by phone on a weekly basis. In the course of this conversation, the psychotherapists address the content from Table 1 in a structured manner. A special focus lies on discussing and reviewing the accomplishment of the exercises incorporated in each module*.* In a 1-h training session, all clinical psychologists who were interested in accompanying subjects were informed. The training included general information on the study, risks and handling of these risks, a discussion of the non-accident concept, instructions on the handling and documentation of drop-outs and information on the standardization of the discussion content.

